### Sample size

The study primarily wishes to demonstrate a statistically significant difference in the two subscales of the 12 items Short Form (SF-12)^20^ measuring health-related quality of life, and in the five participating countries. Based on a study on the effect of the CDSMP in lumbar back pain, the subscores ‘well-being’ and ‘energy’ of the SF-36 improved by 6.0±19.1 and 4.3±23.2, respectively, after 6 months.^21^ The lowest Cohen’s d is therefore of 0.185 in quality of life domains. Thus, the principal conclusion of the study will rely on 10 tests. Applying the Bonferroni’s correction on the significance threshold, we will consider an alpha risk of 0.005 for the tests measuring the quality of life (self-rated with SF-12) in vulnerable patients with chronic diseases and caregivers. To show a statistically significant effect size of 0.185, by a paired Student’s t-test, with a bilateral alpha risk of 0.005, a power of 0.9 and a correlation between baseline and 6 months of 0, we need to analyse 978 subjects. Assuming a drop-out rate of 20%, we need to include at least 1223 subjects. The multicentre study will include 2000 subjects (400 per country), which will bring about sufficient power to analyse the objectives.

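### The ten principal SF-12 tests are held to single-step Bonferroni at 0.005; this is valid, but Holm's step-down gives the same 5% familywise control and never fewer detections

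*Protocol article*

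**What the plan says.** The Sample size section of the protocol article sets the primary aim as a significant difference in both SF-12 subscales "and in the five participating countries". It then states: "Thus, the principal conclusion of the study will rely on 10 tests". Two subscales in five countries give the ten. A Bonferroni correction follows, and its wording attaches the threshold to the tests themselves: "correction on the significance threshold, we will consider an alpha risk of 0.005 for the tests measuring the quality of life". The same level enters the planning calculation, "with a bilateral alpha risk of 0.005, a power of 0.9 and a correlation between baseline and 6 months of 0", which yields 978 subjects to analyse and 1223 to include.

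The Statistical analysis plan section does not replace this rule. For multiplicity it names one-way analysis of variance with Bonferroni-type post hoc testing, and it has the analyses repeated by country. Neither section mentions a stepwise procedure or gives a reason for needing the single-step form.

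**The concern.** With a fixed level of 0.005, a country result at p = 0.006 fails even if the other nine tests are overwhelmingly significant. Holm relaxes the threshold after each rejection and keeps the familywise error at 5%, so the fixed rule gives up detections that the same error budget would allow. The loss is largest when the programme works in most countries.

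The country results carry the principal conclusion. The Guidelines and policy recommendations section also draws its recommendations from the results of the participating countries, although it does not tie them to a significance threshold.

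**Working it through.** **Inputs from the protocol article, Sample size section.** Ten tests; effect size 4.3/23.2 = 0.185; two-sided alpha 0.005; power 0.90; baseline-to-6-month correlation 0; 20% drop-out; 400 subjects per country. If the 400 are counted before drop-out, 400 × 0.8 = 320 are analysed. The Study population section instead describes 2000 as the number who finish and are evaluated, which gives 400 analysed. Both are shown.

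**Assumption not in the document.** The correlation between the two subscales within a country is set to 0 and then 0.3. Results barely differ.

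**Step 1: the plan's own figures.**
- Per-test level: 0.05/10 = 0.005.
- With correlation 0, the SD of the change is SD × √2, so n = 2 × ((2.807 + 1.282)/0.185)² ≈ 977 by the normal approximation and 981 by the noncentral t. The stated 978 reproduces.
- Drop-out: 978/0.8 = 1222.5, so 1223. This reproduces.

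**Step 2: power of one country-level test at 0.005.**
- 400 analysed: 0.185 × √(400/2) = 2.616, and Φ(2.616 − 2.807) = Φ(−0.191) ≈ 0.42.
- 320 analysed: 0.185 × √(320/2) = 2.340, and Φ(−0.467) ≈ 0.32.

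**Step 3: the two rules.** Bonferroni compares every p-value with 0.005. Holm orders the p-values and compares them in turn with 0.05/10, 0.05/9, …, 0.05/1, that is 0.005, 0.00556, 0.00625, 0.00714, 0.00833, 0.01, 0.0125, 0.01667, 0.025 and 0.05, stopping at the first failure. No Holm threshold is below 0.005, so every Bonferroni rejection is also a Holm rejection.

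**Step 4: simulation** (200,000 trials per scenario, ten z-tests, five independent countries with two subscales each, correlation between baseline and 6 months 0, d = 0.185 for each true effect).

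| Analysed per country | Effects real | Bonferroni | Holm | Trials with at least one extra detection |
|---|---|---|---|---|
| 400 | 10 of 10 | 4.2 | 5.1 | 51% |
| 400 | 5 of 10 | 2.12 | 2.25–2.26 | 12% |
| 320 | 10 of 10 | 3.2 | 3.7–3.8 | 36% |
| 320 | 5 of 10 | 1.60 | 1.69–1.70 | 8–9% |

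Average power per test at 400, with all ten real, goes from 0.42 to 0.51. Detecting all ten goes from below 0.1% to 3–4%. Holm lost no Bonferroni rejection in any simulated trial.

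**Step 5: one real effect.** Holm can help that effect only after a null test has been rejected at 0.005. For nine independent nulls that has probability 1 − 0.995⁹ ≈ 0.044. Even then the threshold typically moves only from 0.005 to 0.00556. The gain is negligible.

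**Step 6: error control.** With all ten effects null, familywise error is 4.8% under both rules. With five null it is about 2.5% under Bonferroni and 3.0–4.4% under Holm across the scenarios run, including those at correlation 0.5. All are within 5%.

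**The case against.** **Bonferroni at 0.005 is not an error.** This stands. It is prespecified and controls the familywise error, so the point concerns efficiency only. Nor is the gain wholly free: single-step Bonferroni comes with simple simultaneous intervals, and Holm-compatible ones are less simple. The document does not invoke that advantage.

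**The threshold sits in a sample-size paragraph, and a step-down refinement could be left to an unseen analysis plan.** This stands only in part. The wording assigns 0.005 to the tests on which the conclusion rests, and the analysis section again names only a Bonferroni-type adjustment.

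**The main tests may be pooled.** The Statistical analysis plan section describes overall analyses first and country analyses as additional, and the Sample size section sets 978 against a total of 2000. For a pooled test of 2000 at 0.005, power is about 99.9%, so Holm would add almost nothing. But the ten tests arise naturally only as two subscales by five countries, and that is the family the article names. The two sections should be reconciled in any case.

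**Stronger readings that the document does not support.**
- A reader might infer that the chance of all ten being significant rises from 13–15% to 63–64%. That requires all ten effects to be real and 0.185 to be change divided by the SD of change (equivalent to a correlation of 0.5), whereas the plan states a correlation of 0. On the plan's inputs the rise is from below 0.1% to 3–4%.
- A reader might infer that each test could be run at 0.05, as one claim that all ten succeed. A Bonferroni correction implies separate claims, and so do country-specific recommendations. For ten independent nulls, separate claims at 0.05 would carry a familywise error of 1 − 0.95¹⁰ ≈ 40%.
- A reader might infer that Holm repairs country-level power. It does not: average power reaches only about 51% at 400 per country, even with all ten effects real.

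**Conclusion.** The point holds as an avoidable inefficiency in a stated rule. Holm's advantage needs no assumption about dependence between the tests. Its size does depend on assumptions: at 400 analysed per country, d = 0.185 and correlation 0, the gain is about 0.9 detections of 10 if all effects are real, about 0.13 of 5 if half are, and close to nothing if one is. At 320 with all ten real it is about 0.55 of 10.

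The main reason that country gains would be missed is the shortfall of 400 per country against the 978 that one test needs. The multiplicity rule is secondary, but it can be improved at almost no cost.

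**What to change.** Leave 0.005 in the planning calculation; Holm's first step is also 0.005, so 978 and 1223 do not change. Before any outcome data are seen, state that the ten SF-12 p-values will be judged by Holm's step-down at familywise 0.05, and report Holm-adjusted p-values with 99.5% confidence intervals beside them. Add that the adjusted p-value decides, since a Holm rejection with an unadjusted p above 0.005 will have a 99.5% interval that includes zero. Amend the multiplicity wording in the Statistical analysis plan section so that it names the same ten-test family and the same procedure.

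The cost is a few sentences, with no change to recruitment, data collection or sample size. The only loss is the simplicity of matching simultaneous intervals. The country-level power shortfall has to be addressed separately.

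### The sample size puts a zero correlation on top of an effect size that reads as mean change over SD of change; on that reading 491 subjects per test are needed, not 978

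*Protocol article*

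**What the plan says.** All the inputs are in the Sample size section of the protocol article. In a study of the same programme in lumbar back pain, two SF-36 subscores "improved by 6.0±19.1 and 4.3±23.2, respectively, after 6 months". From the weaker of the two the authors conclude: "The lowest Cohen’s d is therefore of 0.185 in quality of life domains". That is 4.3/23.2.

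The main aim covers two SF-12 subscales in five countries, so "the principal conclusion of the study will rely on 10 tests", and the Bonferroni threshold is 0.05/10. The calculation is made "by a paired Student’s t-test", "with a bilateral alpha risk of 0.005", with power 0.9 and "a correlation between baseline and 6 months of 0, we need to analyse 978 subjects". The section continues: "Assuming a drop-out rate of 20%, we need to include at least 1223 subjects". It then fixes enrolment at 2000, or 400 per country, and calls the power adequate for the objectives.

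**The concern.** A paired t-test depends only on the mean within-person change and the SD of that change. Their ratio is the paired effect size. The baseline-to-follow-up correlation is needed only when the SD to hand describes scores at one time point and has to be converted to an SD of change. If the quoted SD already belongs to the change, the correlation is already inside it and must not be applied again.

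The section reports an improvement with a ± and then also supplies a correlation. Unless 23.2 is a single-time-point SD, these two steps do not fit together, and 978 (hence 1223) does not follow from the cited figures. The plan's stated sample size is at stake. So is the power of the ten country-by-subscale tests for which alpha was set at 0.005, since that power differs greatly between the two readings.

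**Working it through.** **Inputs (Sample size section).** Mean change 4.3; ± value 23.2; paired t-test; two-sided alpha 0.005; power 0.90; correlation ρ = 0; drop-out 20%; 400 per country.

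**Effect sizes.** 6.0/19.1 = 0.314 and 4.3/23.2 = 0.1853. The smaller is the protocol's 0.185.

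**Formula.** If d uses a single-time-point SD (taken as equal at both times), the paired effect size is dz = d/√(2(1−ρ)). If d already uses the SD of change, dz = d. Required n is the smallest n at which the noncentral t, with n−1 degrees of freedom and noncentrality dz·√n, gives 90% power at two-sided 0.005.

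**Step 1: reproduce the protocol.** With ρ = 0, dz = 0.1853/√2 = 0.1311 and n = 978, exactly as stated. (With d rounded to 0.185, n = 981.) Drop-out: 978/0.8 = 1222.5, so 1223, also as stated. The protocol therefore did divide by √2, which implies an SD of change of 23.2 × √2 = 32.8.

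**Step 2: 23.2 as the SD of change.** dz = 0.1853. The normal approximation gives ((2.807 + 1.282)/0.1853)² ≈ 487, and the exact t gives n = 491. Drop-out: 491/0.8 = 613.75, so 614. The ratio is 978/491 = 1.99. At n = 978 this dz has power 99.85%.

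**Step 3: 23.2 as a single-time-point SD.** The result depends on ρ. The non-zero values below are illustrative assumptions, not protocol figures.

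| ρ | n analysed |
|---|---|
| 0 | 978 |
| 0.25 | 734 |
| 0.5 | 491 |

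At ρ = 0.5 the factor 2(1−ρ) equals 1, so the result matches step 2.

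**Step 4: power per country-level test (alpha 0.005).** The Study population section treats 2000 as people who finish the programme and are evaluated, which gives 400 analysed per country. The Sample size section treats 2000 as people included; 20% drop-out then leaves 400 × 0.8 = 320.

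| Analysed per country | ρ = 0, as stated (dz 0.131) | 23.2 = SD of change (dz 0.185) |
|---|---|---|
| 400 | 42% | 81% |
| 320 | 32% | 69% |

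**Step 5: one pooled test.** With 2000 analysed, power is 99.88% at ρ = 0 and higher still on the SD-of-change reading.

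**The case against.** The strongest reply is that the protocol made no slip: it disclosed every input, and those inputs give 978 exactly. It calls the ratio Cohen's d and supplies a separate correlation, which suggests that its authors took 23.2 for a score SD. Zero is then the cautious choice among non-negative correlations, and the paired analysis would still benefit from whatever correlation is observed. This part stands. The ± is unlabelled and the cited study is not at hand, so the score-SD reading cannot be excluded. What the reply does not supply is a reason for zero: the section neither calls it conservative nor justifies it.

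A second reply is that any error is on the safe side and changes nothing in conduct. That also stands for enrolment: neither 978 nor 1223 sets the planned 2000, and a pooled test has ample power either way. It does not dispose of the country-level tests, where the two readings give very different power.

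A reader might infer that 978 is wrong whichever SD is meant, or that the study is too small overall. The document supports neither. On the score-SD reading 978 is correct for its stated inputs, and on the change-SD reading the requirement falls. Nor does the document give any basis for choosing a particular non-zero correlation.

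**Conclusion.** The point holds conditionally. On the natural reading of the improvement figures, the correlation is applied to an SD that already contains it, and the requirement is overstated by a factor of 1.99: 491 analysed (614 enrolled) per test in place of 978 (1223). On the other reading, 978 is a correct but unexplained worst-case bound. The protocol does not say which reading applies, and that is the defect to repair.

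The practical consequence lies in the ten tests that carry the principal conclusion. With 400 or 320 analysed per country, power is 42% or 32% on the stated inputs and 81% or 69% on the change-SD reading. None of these reaches the 90% target, so the general assurance about power is not borne out for those tests on either calculation. These figures assume that an effect of 0.185, taken from SF-36 subscores in back pain, carries over to each SF-12 subscale in each country.

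**What to change.** State whether 19.1 and 23.2 are SDs of change or SDs of scores at one time point.

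- If SDs of change: delete the correlation and restate the requirement as 491 analysed and 614 enrolled per test.
- If score SDs: keep 978 and label it as a conservative bound, or justify a non-zero correlation and show n over a stated range.

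In either case, replace the general assurance about power with the power of the ten country-by-subscale tests at the per-country number, and say whether 400 means enrolled or analysed. Enrolment of 2000 need not change. The cost is one recalculated paragraph and a less favourable statement of country-level power.

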### Statistical analysis plan

Differences between baseline and follow-up measurements will be assessed employing the paired T-test (for normally distributed variables), the Mann-Whitney U test (for variables not normally distributed) and the Pearson χ^2^ test (for variable fractions). To adjust for multiple testing, one-way analyses of variance with post hoc testing (type Bonferroni) will be performed. The relationship of an outcome measure (T1) with explanatory variables will be determined using ordinary least squares regression analysis. The outcome measure (T0), (change in) other outcome measures, risk factors and social determinants may serve as explanatory variables. Additionally, the above-mentioned analyses will be repeated for each country separately and possibly for other subgroups (for variables which are likely to influence the effect of the intervention itself, eg, age and gender). All data from each of the five pilot sites will be anonymised and centralised at one study site for statistical analysis. Analyses will be performed with SPSS V.25.0.

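### The 978-subject requirement applies to each of ten country-level tests but is compared with the pooled 2000; at 400 per country, power is about 42% under the plan's own inputs

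*Protocol article*

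**What the plan says.** All the planning figures are in the protocol's Sample size section. The aim is given as "The study primarily wishes to demonstrate a statistically significant difference in the two subscales of the 12 items Short Form", "measuring health-related quality of life, and in the five participating countries". It continues: "Thus, the principal conclusion of the study will rely on 10 tests". After a Bonferroni correction, "we will consider an alpha risk of 0.005 for the tests measuring the quality of life".

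The effect size comes from a study of the same programme in low back pain, with 6-month improvements of 6.0±19.1 and 4.3±23.2 on two SF-36 subscores: "The lowest Cohen’s d is therefore of 0.185 in quality of life domains". The calculation is for a paired t-test "with a bilateral alpha risk of 0.005, a power of 0.9 and a correlation between baseline and 6 months of 0". It gives 978 subjects to analyse, or 1223 to include with 20% drop-out. The section ends: "The multicentre study will include 2000 subjects (400 per country), which will bring about sufficient power to analyse the objectives".

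Two other sections bear on this. Study population describes the 2000 as people who complete the programme and are evaluated, with at least 2500 recruited. Statistical analysis plan lists the methods and adds that "the above-mentioned analyses will be repeated for each country separately".

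**The concern.** Two subscales in five countries is the only route in the text to ten tests, and it matches the alpha: 0.05/10 = 0.005. A pooled analysis of two subscales would give two tests, not ten. Each of the ten tests therefore uses one country's participants. The 978 is the requirement for one test at that alpha, so it should be compared with the 400 per country. The protocol compares it with 2000.

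At stake is how country results will be read. The Guidelines and policy recommendations section intends to base its recommendations on the results of the individual countries. If power per country is well below the stated level, a non-significant result in one country could be taken as failure of the programme there when the assumed effect is present.

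**Working it through.** **Inputs, all from Sample size unless noted**
- Effect size d = 4.3/23.2 = 0.1853, given as 0.185. The other subscore gives 6.0/19.1 = 0.314.
- Two-sided alpha 0.005, power 0.90, correlation ρ between baseline and 6 months = 0.
- 400 per country. Study population supports reading these as analysed subjects: 2000 evaluated / 5 = 400.

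**Step 1: reproduce the plan's figure.** For a paired test the standardised change is dz = d/√(2(1−ρ)). At ρ = 0, dz = 0.185/√2 = 0.1308. By normal approximation, n = ((2.807 + 1.282)/0.1308)² ≈ 977. The noncentral t gives 981 with d = 0.185 and 978 with the unrounded 0.1853. Drop-out: 978/0.80 = 1222.5, rounded up to 1223. Both stated figures reproduce, so the arithmetic for a single test is sound.

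**Step 2: power of one country-level test at n = 400, same inputs.** dz·√n = 0.1308 × 20 = 2.616. Normal approximation: Φ(2.616 − 2.807) = Φ(−0.191) = 42.4%. Noncentral t: 41.9%. If every true effect equals 0.185, the expected number of significant tests is 10 × 0.419 ≈ 4.2.

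**Step 3: detectable effect.** For 90% power at n = 400 and ρ = 0, d = (2.807 + 1.282) × √(2/400) = 0.289, against the planned 0.185.

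**Step 4: sensitivity to the correlation** (noncentral t, d = 0.185, alpha 0.005)

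| ρ | dz | Power, n = 400 | Power, n = 320 |
|---|---|---|---|
| 0 | 0.131 | 42% | 32% |
| 0.25 | 0.151 | 58% | 45% |
| 0.5 | 0.185 | 81% | 69% |
| 0.6 | 0.207 | 90% | 81% |

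The 320 column is 400 × 0.80 and applies only if the 400 are counted before drop-out. The ρ = 0.5 row also covers the case where ±23.2 is the SD of change, because then dz = 0.185 directly. The correlation that gives 90% power is about 0.59 at n = 400 and 0.67 at n = 320.

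**Step 5: what 90% per country would take at ρ = 0.** 5 × 978 = 4890 analysed, or 5 × 1223 = 6115 included.

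**Step 6: the pooled comparison.** One pooled test at alpha 0.005, ρ = 0 and n = 2000 has 99.9% power. With only two pooled tests, alpha is 0.05/2 = 0.025 each. The noncentral t then needs 728 analysed (726 with unrounded d), and power exceeds 99% at both n = 1600 and n = 2000.

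**The case against.** The strongest reply is that a correlation of 0 is a very cautious input for scores from the same people, so 42% is close to a worst case. The wording of the source result also allows ±23.2 to be the SD of the improvement, in which case power is about 81%. This stands as a limit on the size of the shortfall. It does not rescue the statement, because the plan fixes the correlation at 0, justifies no other value, and 81% is still below the 90% target.

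A second reply is that 0.185 is the smaller of two source effects. At 0.314, power at n = 400 is about 95% even with correlation 0. That is true, but the plan chose 0.185 as its planning value.

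Some stronger readings are not supported:
- A reader might infer that most country results will be non-significant even if the effect is real. That follows at correlation 0, but not where power is 69% to 81% or more.
- A reader might infer that all ten tests must succeed and multiply the powers together. The plan sets no such rule, and Bonferroni correction serves claims made test by test. The two subscales also come from the same participants, so the tests are not independent.
- A reader might see a flat contradiction between Sample size and Statistical analysis plan. The latter never calls the pooled analysis primary, and repeating the analyses by country supplies the country tests. It leaves the primary level unclear and no more.
- A reader might take 320 as the number per country, because Sample size speaks of including 2000 just after using the same verb for the number before drop-out. Study population points to 400 analysed.

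**Conclusion.** The point holds in conditional form. The protocol derives a correct sample size for one test, then declares power sufficient by comparing it with the pooled total when its ten principal tests each have 400 subjects. Under its own inputs (d = 0.185, correlation 0, two-sided alpha 0.005, 400 analysed per country), power per test is about 42% against the 90% planned. It rises to about 81% with a correlation of 0.5 or if the quoted SD is that of change, and reaches 90% only with a correlation near 0.6. If the 400 were counted before drop-out, contrary to Study population, the figures are about 32% at correlation 0 and 69% at 0.5. The conclusion rests on reading the ten tests as two subscales by five countries, which is the only reading that the text offers. It does not show that the study is too small for a pooled conclusion; pooled power is ample.

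**What to change.** **Minimum change.** Replace the closing statement of Sample size with the power per country and subscale at n = 400: about 42% under the stated correlation of 0, with a detectable d of about 0.29 at 90% power. Add the power under an alternative correlation, with its justification, and say whether ±23.2 is the SD of change. State in both Sample size and Statistical analysis plan which level, pooled or country, carries the principal conclusion.

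**Option, if the sponsor accepts a change of aim.** Make the two pooled SF-12 tests primary at 0.025 each (726 to 728 analysed needed; over 99% power at 1600 to 2000). Report country results as secondary, with confidence intervals. This gives up the stated aim of demonstrating a difference in the five countries, so it is a choice for the sponsor and not a correction that the arithmetic forces.

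**Cost.** Rewording of two sections, and a less favourable statement of country-level power. No extra participants in either case.
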